## Abstract

**Background:** Approximately half of U.S. adults have ≥1 cardiovascular disease (CVD) risk factors. Exercise is universally recommended as a first-line lifestyle therapy to prevent and treat CVD. **Objective:** We will conduct a feasibility and pilot efficacy randomized controlled trial to test the usability and user satisfaction of an evidence-based digital health tool we developed for physicians—the *P*rioritizes *P*ersonalizes *P*rescribes *EX*ercise algorithm (P3-EX)—to treat patients with CVD risk factors (ClinicalTrials.gov: NCT07238556). **Methods:** We will recruit 24 physicians who do not prescribe written exercise prescriptions (ExRx) from two local CT hospitals. Physicians will recruit two patients each (N = 48); both patients must have CVD risk factors. Each physician will deliver a P3-EX ExRx to one patient (n = 24) and the Physical Activity Vital Sign ExRx to the other patient (n = 24) in a random sequence crossover design. Physicians and patients will rate the feasibility and acceptability of each ExRx method using validated questionnaires. Patients will perform their ExRx for 12 weeks and complete an exercise diary to monitor exercise adherence with weekly virtual oversight by Research Assistants. Before and after the exercise intervention, we will measure patient CVD risk factors and physical activity levels via accelerometry. **Results:** This trial has received Institutional Review Board approval (E-HHC-2025-0198) and will begin in January 2026, with findings published in 2027. **Conclusions:** This protocol provides the scientific rationale and methodology to test P3-EX within a real-world clinical setting, to inform the feasibility of using P3-EX as a digital health support tool by physicians, and preliminary efficacy of P3-EX to improve patient cardiovascular health and physical activity levels.

## 1. Introduction

### 1.1. Background

Cardiovascular disease (CVD) is the most prevalent and costliest chronic disease worldwide, accounting for one in four deaths per year in the U.S. [1]. The direct healthcare costs associated with CVD are projected to rise from USD 393 billion in 2020 to USD 1490 billion by 2050 [2]. Approximately half of U.S. adults have one or more of the major CVD risk factors of obesity, hypertension, dyslipidemia, and diabetes [1]. Due to the numerous health benefits of physical activity (PA) [3], professional organizations such as the American College of Sports Medicine (ACSM) and American Heart Association (AHA) recommend exercise as a first-line lifestyle therapy to prevent and treat CVD and its risk factors [4,5]. However, only about 25% of U.S. adults meet the PA recommendations of 150 min per week of moderate and/or 75 min per week of vigorous intensity aerobic exercise or a combination of both and 2 days per week of resistance exercise [6].

To address these significant public health challenges, there is an urgent call for clinicians to recommend PA to their patients [7]. Although a standard of care for PA recommendation is not established in medical practice, the ACSM advocates for clinicians to assess and prescribe PA as a vital sign (PAVS) in routine medical visits with every patient [8,9]. Indeed, a physician’s recommendation to exercise provides their patients with a strong incentive to be physically active [10,11]. However, only about 20% of U.S. adults and 44–56% of patients with CVD risk factors report being advised by their healthcare providers to exercise [12,13]. When they are advised, 80% of them are recommended to walk [14]. Although physicians are receptive to prescribing exercise and counseling their patients to exercise [15,16], they encounter barriers to do so such as a lack of time, training, confidence, and tools [17,18].

Exercise prescription (ExRx) is the process of structuring an individualized PA program by the *F*requency (How Often?), *I*ntensity (How Hard?), *T*ime (How Long?), and *T*ype (What Kind?) principle of exercise or FITT [19]. Personalized ExRxs are preferred to generic approaches because (1) they optimize effectiveness and minimize adverse effects [20,21]; (2) consider patient preferences and goals [22]; (3) align with patient-centered care [23]; and (4) inform shared decision making [24]. For these reasons, the ACSM recommends individualized FITT ExRxs for 26 different chronic diseases and health conditions that include the major CVD risk factors of obesity, hypertension, dyslipidemia, and diabetes [25,26,27,28].

The use of digital health tools has grown significantly among physicians due to their increased efficiency for providing clinical decision support and remote care for their patients [29]. Digital health tools show promise as clinical decision support systems to guide physicians in prescribing exercise to their patients with chronic diseases and cardiovascular disease risk factors [30,31]. [name], assisted by [name], has developed a clinical decision support tool that *P*rioritizes *P*ersonalizes *P*rescribes *EX*ercise (P3-EX) [32]. P3-EX includes (1) the ACSM exercise preparticipation health screening recommendations to determine if there is a need for medical clearance [33]; (2) an adapted AHA Life’s Essential 8 [34] cardiovascular health scoring system to determine the CVD risk factor posing the greatest risk [22]; and (3) the ACSM strategies for designing an ExRx for people with multiple CVD risk factors [25] to produce a prioritized FITT ExRx framed for the CVD risk factor posing the greatest risk. P3-EX is evidence-based, being founded on the ACSM and AHA ExRx standards, is time efficient, and enables clinicians with no ExRx training to produce personalized ExRx for their patients, to optimize their cardiovascular health [32]. The novelty of the P3-EX algorithm meets an unmet clinical need and unique market niche [35].

### 1.2. Objectives

What remains to be carried out is a feasibility and pilot efficacy randomized control trial (RCT) to test the usability and user satisfaction of P3-EX in a real-world clinical setting. Our primary aim is to evaluate the feasibility and acceptability of P3-EX for physicians to use to prescribe exercise to patients with CVD risk factors. Our secondary aim is to explore the preliminary efficacy of P3-EX to improve the patient CVD risk factors of blood pressure, body composition, blood lipid-lipoproteins and glucose, objective and subjective PA levels, and exercise adherence. We hypothesize P3-EX will be feasible for physicians to use to prescribe customized exercise routines for patients with CVD risk factors, and they and their patients will be satisfied with P3-EX. We also hypothesize that P3-EX will result in favorable improvement trends in patient CVD risk factors, PA levels, and exercise adherence.

## 2. Materials and Methods

This study is named the *P3-EX Feasibility Trial* and is reported accordingly with Standard Protocol Items from the Recommendations for Interventional Trials 2025 checklist [36], available as Supplementary File S1. This trial was registered on ClinicalTrial.gov (NCT07238556; https://clinicaltrials.gov/study/NCT07238556) on 19 November 2025. The trial will be managed by Co-Principal Investigators [name], [name], and [name]; Co-Investigators [name], [name], [name], and [name]; a Student Investigator and Graduate Research Assistant [name]; and University of Connecticut (UConn) Research Assistants (RAs). Their planned roles are specified throughout the Materials and Methods (Section 2) and listed under Author Contributions.

### 2.1. Trial Design

The P3-EX Feasibility Trial is a feasibility and pilot efficacy RCT with a two-arm crossover exploratory design (Figure 1). Physicians (N = 24) will be individually randomized with a 1:1 allocation ratio to deliver P3-EX to one of their patients (n = 24) and PAVS to another patient (n = 24) in random sequence. Because physicians will deliver P3-EX and PAVS to patients during their routine healthcare appointments that are scheduled in advance of their enrollment, we will not implement a washout period for physicians between their delivery of P3-EX and PAVS, but will control for potential period or carryover effects in statistical analyses.

### 2.2. Trial Setting

Physicians and patients will be recruited from primary care, outpatient community, and hospital settings in CT, U.S. [name] will conduct enrollment and data collection at two local hospital clinics in Hartford and Farmington, CT, U.S. [37,38]. Physicians will deliver P3-EX and PAVS at the medical setting where they practice, and patients will perform an unsupervised exercise intervention at a setting of their preference. There is no planned patient or public involvement to inform the design, conduct, or reporting of the trial.

### 2.3. Eligibility Criteria

The inclusion and exclusion criteria for physicians and patients are listed in Table 1. We will recruit primary care physicians and preventive care specialists, and their patients who will be physically inactive healthy adults with ≥1 CVD risk factor. Patients will agree to maintain their medication routine and habitual diet and not follow other exercise or nutrition programs.

### 2.4. Physician and Patient Recruitment and Enrollment

[name], [name], and [name] will email their physician colleagues, and physicians will be notified using listservs and newsletters distributed by Hartford HealthCare, UConn Storrs, and UConn Health. Flyers and leaflets will be used at the hospital clinics and community locations. Physicians will complete an online screener and attend a one-on-one virtual study orientation visit led by [name] and an RA over Microsoft Teams to provide consent; confirm eligibility; provide demographics including age, gender, ethnicity, medical specialty, the number of years in practice, prior experience using digital health tools; assess barriers to and confidence with ExRx and PA levels; be orientated to the study procedures; and receive brief ExRx delivery training regarding their patients. [name] will use a standardized script from our laboratory to verbally and uniformly train physicians on the study procedures to deliver the P3-EX and PAVS ExRxs, detailed in their ExRx Instruction Manual (Supplementary File S2), and physicians will not practice using P3-EX or PAVS prior to using each ExRx method.

The enrolled physicians will identify patients who have upcoming appointments with them through the hospitals’ scheduling or electronic medical record systems. Physicians will briefly screen health history profiles of their upcoming patients using the study inclusion criteria. Physicians will inform patient candidates by uploading an electronic flyer to their MyChart account and by phone call. Patients will complete a phone screening and attend two one-on-one in-person study visits led by [name] and an RA to provide consent; confirm eligibility; provide demographics including age, sex, gender, ethnicity, education level, household composition, salary, and technology use; and undergo pre-intervention assessments of PA levels and CVD risk factors.

### 2.5. Physician Randomization

#### 2.5.1. Sequence Generation

We will use block randomization [43] to assign the ExRx delivery sequence among physicians (N = 24), stratified by those who meet the PA guidelines [44] (n = 12) and those who do not meet them (n = 12). Within each PA level, physicians will be randomly assigned to one of two delivery sequences using permuted blocks of four: (1) P3-EX followed by PAVS, or (2) PAVS followed by P3-EX. This approach aims to ensure equal allocation of the ExRx delivery sequences across PA levels to control for the potential confounding effect of physician PA levels on the primary aim of the study [45].

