#### 2.5.3. Blinding

[name], who will conduct physician and patient enrollment and pre- and post-intervention outcome assessments, will not have access to the random allocation sequence. [name] will be blinded to group assignments during patient pre-intervention outcome assessments, and laboratory technicians will be blinded when assessing all blood lipid-lipoprotein and glucose values. Patients will disclose details of their healthcare appointment to [name] after completing all pre-intervention outcome assessments.

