### 4.3. Limitations

We acknowledge potential limitations with the P3-EX Feasibility Trial. Physicians may experience burden of recruiting two of their patients to participate in the study. However, given that preventive care is one of the most common reasons for office-based physician visits [81], we anticipate that a high proportion of patients will be eligible. Concerning blinding, other than laboratory technicians assessing blood lipid-lipoproteins and glucose, we will not include other blinded outcome assessors. [name] will have knowledge of patient group assignments when conducting patient exercise guidance virtual visits and assessing vitals, body composition, and objective and subjective PA levels at post-intervention. [name] will therefore follow standardized laboratory operating procedures [59,65,66] to minimize observer bias, which include following outcome measurement protocols, providing privacy to patients during in-person survey completions, and reading standardized exercise guidance scripts. Although the TLFB-E is potentially susceptible to social desirability bias, we will cross reference the TLFB-E with the accelerometer at pre- and post-intervention. Last, concerning the study design, the trial does not include a non-exercise control group, which may hinder the ability to interpret the efficacy of P3-EX for improving patient PA levels or CVD risk factors. Nonetheless, this pilot data will inform the efficacy of P3-EX compared to generic ExRx approaches in routine medical care.

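### A single published block size of four lets the role that enrols and measures at baseline deduce some first patients' arms in advance; how many depends on recruitment timing, which the protocol does not state

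*Protocol article*

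**What the plan says.** All references are to the protocol article.

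- **Randomisation.** Section 2.1 has physicians "individually randomized with a 1:1 allocation ratio". Section 2.5.1 stratifies them by whether they meet the physical activity guidelines, 12 in each stratum, and adds that "physicians will be randomly assigned to one of two delivery sequences using permuted blocks of four". The sequences are P3-EX then PAVS, or the reverse, with one patient per method.
- **Concealment.** Section 2.5.2 gives the list and the sealed, numbered envelopes to a role outside data collection. The physician learns the sequence after the first patient is enrolled.
- **Who enrols and measures.** Section 2.5.3 describes one role "who will conduct physician and patient enrollment and pre- and post-intervention outcome assessments, will not have access to the random allocation sequence". That role is to be blinded during pre-intervention assessments.
- **What that role sees.** Section 2.4 collects the physician's activity level at the orientation visit where consent is taken, so the stratum is visible. Patients then "attend two one-on-one in-person study visits" for consent, eligibility and baseline. Under Section 2.5.3, "Patients will disclose details of their healthcare appointment to" the assessor "after completing all pre-intervention outcome assessments". Section 4.3 adds that the assessor "will have knowledge of patient group assignments when conducting patient exercise guidance virtual visits".

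**The concern.** Envelopes and lack of list access protect against reading the list. They do not protect against inferring it. Each physician treats one patient with each method, so one disclosed arm reveals that physician's whole sequence. Someone who knows the stratum, the block size and the earlier sequences can sometimes fill in the next one. That tells them the arm of the next physician's first patient before that patient consents or is measured, and before the physician has been told anything.

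The baseline blinding stated in Section 2.5.3 would then fail for those patients. The same role confirms eligibility and measures blood pressure, waist, height and weight at baseline. Section 4.3 concedes unblinding at the guidance visits and post-intervention only, so this route is not acknowledged. What could be biased is the between-arm patient comparison, whose data Section 5 intends to use to power a larger trial.

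**Working it through.** **Inputs.** Block size 4, ratio 1:1, two strata of 12 (Sections 2.1 and 2.5.1). The recruitment target follows from Section 2.13: 19/0.8 = 23.75, rounded up to 24 physicians; 38/0.8 = 47.5, rounded up to 48 patients. Each stratum therefore holds 12/4 = 3 whole blocks, 6 in all. The protocol gives no predictability figure to reproduce.

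**Assumption.** The documents do not say how physicians overlap in time. I therefore vary the number of immediately preceding physicians in the stratum whose sequence the assessor does not yet know: 0, 1, 2 or 3.

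**Blocks of four, all predecessors known.** The six equally likely orders are AABB, ABAB, ABBA, BAAB, BABA and BBAA.

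- Place 1: never certain; best guess right 1/2.
- Place 2: never certain; best guess right 2/3, since two of the three remaining slots are the other sequence.
- Place 3: certain if the first two agree (2/6 = 1/3), otherwise even. Best guess right 1/3 × 1 + 2/3 × 1/2 = 2/3.
- Place 4: always certain.

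Certain per block: 1/3 + 1 = 4/3, so (4/3)/4 = 33.3%, and 6 × 4/3 = 8 of 24 expected. Each block gives 1 or 2, so the range is 6 to 12. Best guess: (1/2 + 2/3 + 2/3 + 1)/4 = 70.8%.

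**One predecessor masked.** Place 3 is guessed from place 1 only, and place 4 from places 1 and 2. Certain: (1/3)/4 = 8.3%, and 6 × 1/3 = 2 of 24. Best guess: (1/2 + 1/2 + 2/3 + 2/3)/4 = 58.3%.

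**Two masked.** Only place 4 carries information. Certain: 0%. Best guess: (3 × 1/2 + 2/3)/4 = 54.2%.

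**Three masked.** 0% and 50%.

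**Alternatives.** Every possible order of 12 was enumerated with its probability; for varying sizes the observer is assumed to know which sizes are possible but not their order. Cells show the share certain / best-guess accuracy.

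| Predecessors masked | Fixed 4 | Random 2/4/6 | One list of 12 |
|---|---|---|---|
| 0 | 33.3% / 70.8% | 3.4% / 69.3% | 14.3% / 64.3% |
| 1 | 8.3% / 58.3% | 2.0% / 56.8% | 6.0% / 60.1% |
| 2 | 0% / 54.2% | 0.7% / 54.1% | 2.2% / 58.2% |
| 3 | 0% / 50% | 0% / 51.3% | 0.6% / 56.3% |

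**Balance.** If a stratum stops at 8, fixed blocks of four always give 4:4. A list of 12 gives 4:4 with probability C(6,4)²/C(12,8) = 225/495, so it is unequal in 54.5% of cases. With random 2/4/6, the chance that the 12th physician falls two places into a block of 4 is 121/729, two places into a block of 6 is 121/729, and four places into a block of 6 is 111/729. The split is then unequal with probability 1/3, 2/5 and 2/5 respectively: (121/729)(1/3) + (232/729)(2/5) = 18.3%, and never worse than 7:5.

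**The case against.** The strongest objection is timing. For a predecessor to be unmasked, a patient must be identified, phone screened, seen at two visits, attend a pre-scheduled appointment and disclose what happened. Section 2.4 approaches physicians together by email, listserv and newsletter, so several in a stratum may be in progress at once. The assessor must also know whether envelopes follow physician or first-patient enrolment order, which Section 2.5.2 leaves open. This stands: a reader might infer that a third of sequences will be predictable, and the documents do not support that.

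The bias route is also narrow. Physicians, not the assessor, choose the patients, and nothing suggests physicians know the block history. The eligibility criteria are largely numeric or listed, and an assistant is present at the visits. Blood pressure comes from an automatic monitor with a numeric agreement rule, blood results are laboratory-blinded, and activity is measured by accelerometer. This limits the consequence but does not restore the stated baseline blinding.

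Third, a larger route exists whatever the block size. The second patient's arm is the complement of the first, and the physician is told after the first patient is enrolled. That is a separate matter. Block predictability reaches the first patient, and withholding assignments until both patients were enrolled would not remove it.

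Finally, fixed blocks of four with independent generation and sealed envelopes are conventional, and they serve the balance that Section 2.5.1 seeks. That is a good reason to reject a single list of 12, which raises guessing accuracy as soon as one predecessor is masked and balances poorly if a stratum stops short. It is a weaker reason against varying the block size.

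**Conclusion.** The point holds as a minor one. The mechanism follows from the protocol's own text: one published block size, a visible stratum, and an enrolling assessor who learns earlier arms. Its size runs from an expected 8 of 24 first patients known with certainty under fully sequential recruitment, through 2 of 24 with one masked predecessor, to none with two or more. Even at the ceiling, about two thirds of first patients' arms are not certain.

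A reader might also infer that the primary result is compromised. It is not to any real degree: each physician delivers both methods, and the one-sample usability test against 4.0 does not depend on foreknowledge of a patient's arm. The exposure is confined to eligibility confirmation and assessor-measured baseline values for the secondary patient comparison. These figures assume that the assessor keeps track of earlier sequences and knows the envelope order; nothing shows that anyone intends to use this knowledge.

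**What to change.** In Section 2.5.1, for physicians not yet randomised, replace the fixed blocks of four with randomly varying block sizes (for example 2, 4 and 6). The independent role that already holds the list should generate them. Sizes and order should be withheld from the enrolling assessor and left unpublished until recruitment closes.

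The gain is mainly in certainty. Certain predictions fall from 33.3% to 3.4% under sequential recruitment and from 8.3% to 2.0% with one masked predecessor, while guessing accuracy drops by about 1.5 percentage points in each case. With two or more masked there is nothing to gain.

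The cost is one protocol sentence, a regenerated list and new envelopes, plus a small imbalance if a stratum ends mid-block: a 7:5 split in about 18% of strata of 12 if sizes are drawn freely. A single list of 12 per stratum should not be used instead.

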#### 2.5.2. Allocation Concealment and Implementation

[name], who is not involved in data collection or outcome assessment to maintain allocation concealment, will create a computer-generated randomization schedule (https://www.sealedenvelope.com/, 30 November 2025) [46] maintained on a university-owned desktop computer with password protection. [name] will prepare sequentially numbered, sealed envelopes in advance, and will only open them after physicians and patients are enrolled. [name] will inform physicians of their random assignment via email after their first patient is enrolled.

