### 2.6. Interventions and Comparators

Each patient will attend their scheduled healthcare appointment with their physician and receive their healthcare as planned and permitted. During each appointment, in random sequence, the physician will deliver P3-EX to one patient and PAVS to the other patient.

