### 2.14. Statistical Analysis

The statistical analysis plan for this trial is accessible on ClinicalTrials.gov. Statistical analyses will be conducted by [name] using Statistical Package for the Social Sciences (version 30, IBM Corp., Armonk, NY, USA) [74] with oversight from [name], [name], [name], [name], and [name], with [name], [name], [name], and [name] being blinded to group assignments. We will first use descriptive statistics and graphical techniques to ensure all test assumptions are met, including the inspection for outliers, normal distributions [75], and homogeneity of variances [76]. Missing values will be addressed using model-based approaches and/or multiple imputations when appropriate to include the entire randomized sample [77]. If normality assumptions are not met for secondary outcomes, considerations will be made to transform the data to achieve a normal distribution or use alternative non-parametric approaches such as permutated tests. An alpha level of 0.05 will be used to determine statistical significance.

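### The envelope fixes the physician's order of use but not which enrolled patient holds which position, so a patient's arm stays open after allocation to a physician who knows the order

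*Protocol article*

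**What the plan says.** Section 2.1 makes the physician the randomised unit: "Physicians (N = 24) will be individually randomized with a 1:1 allocation ratio". Section 2.5.1 names what is allocated: "physicians will be randomly assigned to one of two delivery sequences using permuted blocks of four", the two sequences being P3-EX then PAVS, or the reverse.

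A patient acquires an arm at the visit. Section 2.6 says: "During each appointment, in random sequence, the physician will deliver P3-EX to one patient and PAVS to the other patient". Section 2.1 says that "physicians will deliver P3-EX and PAVS to patients during their routine healthcare appointments that are scheduled in advance of their enrollment", so the trial does not set the visit dates.

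On timing, section 2.5.2 says of the person holding the envelopes that they "will only open them after physicians and patients are enrolled". The same section says that the study team "will inform physicians of their random assignment via email after their first patient is enrolled". Section 2.4 has the enrolled physician identify the patients from upcoming appointments.

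Section 2.14.2 then compares patients as a P3-EX group and a PAVS group over 12 weeks. Section 2.14 aims, through its handling of missing values, "to include the entire randomized sample".

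**The concern.** For the physician ratings, order is the right thing to randomise. The patient comparison needs something else: an arm for each patient, fixed before anything that a person who knows the allocation can influence. Section 2.5 gives each physician a sequence but no rule that converts it into an arm for a given enrolled patient. Between the opening of the envelope and the visit, the patient's arm depends on the calendar, and the physician knows what each position means.

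Two things are at stake. The physician could, knowingly or not, affect who receives which prescription. And a patient who has completed baseline but leaves before the visit may not be countable in either arm. Section 5 intends to use the secondary-outcome data to power a larger trial, so the patient comparison matters beyond this pilot.

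**Working it through.** **Denominators.** Section 2.13 gives d = (4.650 − 4.0)/0.759 = 0.856 and 19 physicians for 85% power at one-sided α = 0.01. A noncentral-t approximation with the Wilcoxon efficiency 3/π gives 84.8% at n = 19. Inflation for 20% attrition gives 19/0.80 = 23.75, so 24 physicians, and 38/0.80 = 47.5, so 48 patients. The sample size is not in question; 24 pairs and 48 patients are used below.

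**What determines a patient's arm.**
1. The physician holds a sequence (2.1, 2.5.1).
2. The sequence is applied at the appointments (2.6).
3. The appointments are routine bookings (2.1).
4. No section says that first means first enrolled, or attaches a study number to a position.

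On the literal text, arm = sequence combined with visit order.

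**When a swap can occur.** Both patients must be enrolled, neither seen, and the visit order must reverse. A later date for the second visit, or any change after the first delivery, swaps nothing.

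**Why re-ordering is plausible.** Before the visit come two in-person study visits (2.4), fasting blood tests at outside centres (2.8.5) and accelerometry with a possible second wear (2.8.7). Enrolment order therefore need not be visit order. P3-EX also needs the patient's risk-factor values (2.6.1), which the study team sends to the physician (2.16.2). PAVS needs screening and activity questions and a handout (2.6.2). It is an inference, not a statement in the article, that late results could give a physician who knows the order a practical reason to exchange two visits.

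**When a swap biases.** The sequence is computer-generated, with a 1:1 ratio. If the reason for re-ordering is independent of the sequence, each patient still has probability 1/2 of either arm, even if the reason relates to prognosis. Bias requires the re-ordering, or the choice of patient, to depend on the sequence. Section 2.5.2 describes telling physicians only, and no section says that patients learn the order before the visit. The route is therefore the physician's knowledge.

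**Size of re-ordering.** The documents give no rate. As assumptions:

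| Share of pairs reversed | Pairs (24 × share) | Patients with changed arm (48 × share) |
|---|---|---|
| 5% | 1.2 | 2.4 |
| 10% | 2.4 | 4.8 |
| 20% | 4.8 | 9.6 |

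A severe case for bias supposes that every reversal moves the better-prognosis patient into the same arm. For two independent normal patients the mean absolute difference is 2/√π = 1.128 SD. A swap turns −1.128 into +1.128, a change of 2.26 SD in that pair. The group difference then shifts by 2.26 × share = 0.11, 0.23 and 0.45 SD. With re-ordering unrelated to the sequence the expected shift is zero.

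**Loss before the visit.** If one patient has been seen, the other's arm follows as the remaining tool. The undefined case is a first patient lost before any delivery, since the text does not say whether the next patient takes that position. At assumed pre-visit loss of 5%, 10% and 20%, first patients lost number about 24 × rate = 1.2, 2.4 and 4.8. The 20% in section 2.13 is patient attrition as a whole, so 20% before the visit is a high assumption.

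**The two sentences on timing.** One opens envelopes after physicians and patients are enrolled; the other informs the physician after the first patient is enrolled. If the second is applied as soon as the first patient is in, the physician can know the order while choosing the second patient.

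**The case against.** The article condenses a fuller protocol, and an instruction manual and an SAP exist that are not shown; the mapping of positions to patients may stand there. The reference to a first enrolled patient in section 2.5.2 fits a reading in which first and second mean order of enrolment. On that reading a moved visit changes nothing. This stands as a possible intention, but no section states it, and sections 2.1 and 2.6 point to the visit. Section 2.5 does describe the allocation mechanism, so what it fixes is open to comment.

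A reader might infer several stronger things, which the documents do not support:
- *That any cancelled or rebooked visit swaps both arms.* It does so only under the three conditions shown above.
- *That re-ordering for patient reasons biases the comparison.* It does not, if unrelated to a concealed sequence.
- *That the aim to include the whole randomised sample cannot be met.* Physicians are the randomised unit, so that sentence can be read as referring to them, and many lost patients' arms can be inferred.
- *That 19% to 36% of physicians would be affected.* With an assumed 10% to 20% of visits moved or missed, 1 − 0.9² = 0.19 and 1 − 0.8² = 0.36, or 4.6 and 8.6 of 24 physicians. That counts physicians with at least one such visit, not swaps.

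It is also fair to say that the sequence is randomised to protect the primary aim, and that binding arms to patients gives up a little of that protection. The fix has to respect this.

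**Conclusion.** The point holds in limited form. As written, section 2.5 leaves the patient's arm to visit order while the physician knows the sequence, and it gives no rule for a first patient lost before delivery. The patient comparison is exposed to bias only through the physician's knowledge of the order; nothing shows that such influence will occur. The number of swaps is unknown, and the counts and SD shifts above rest on assumed rates and, for the shifts, on a severe case. The primary usability ratings rest on the randomised order and are largely unaffected. The conclusion assumes the literal reading of sections 2.1, 2.5.1 and 2.6; a stated rule that position means enrolment order would remove the moved-visit problem. The change should be made because it is cheap and the patient comparison is presented as randomised.

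**What to change.** - **Section 2.5.** Number each physician's two patients at enrolment and bind arm to patient number when the envelope is opened, whatever the later order of visits. Open the envelope and inform the physician only after both patients are enrolled, and reconcile the two sentences in 2.5.2 accordingly.
- **Section 2.14.2.** Analyse patients in the assigned arm, and count those lost before the visit in that arm.
- **Section 2.14.1.** In the physician model, keep the randomised sequence as the main order term. Use actual delivery order in a sensitivity analysis where the two differ.

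The cost is envelope wording and a few sentences. Holding back the order until both patients are enrolled may be awkward where the first patient's visit falls early. In re-ordered pairs the actual delivery order will depart from the randomised one, so sequence balance may be slightly off.
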